### Statistics

For a relative risk reduction of 40% in drug-related hospital readmissions from 19% to 11%, a total study population of 700 individuals is required to achieve a statistical power of 80% at our prespecified significance level of 0.05 for two-sided tests. The estimated incidence of drug-related readmissions was observed in a previous trial within the same community, although that study was limited to elderly people with major NCD.^25^

We will present time-to-event data in Kaplan-Meier survival curves and analyse differences in survival data between the groups through log rank tests and Cox proportional hazard models. Further investigations of subgroup effects and adjustments of the regression models will be based on heart failure and cognitive impairment as prognostic factors. We will analyse secondary outcomes using various appropriate statistical tests, such as X^2^ and independent sample t-test, depending on the type of variable.

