### Study population, recruitment and randomisation

The recruitment of study participants started in September 2019 and takes place among emergency admissions to the University Hospital of Umeå. We will continuously recruit participants until we reach the target sample size of 700 randomised individuals. Thus far, recruitment has been limited to one medical ward; however, it is possible to increase the number of wards if the inclusion rate proves insufficient to reach the target sample size during 2022. People who meet the eligibility criteria are given the opportunity to participate in the trial (box 1). Once written consent has been obtained (approval from next of kin in cases of people with major NCD), the participants report self-assessed adherence and quality of life through questionnaires. Following discharge from the ward, the participants are randomly assigned to one of the two study arms through a stratified randomisation procedure (figure 1) based on their results from a shortened 4-item version of the Gottfries’ Cognitive Scale,^31^ a validated tool for proxy rating cognitive impairment.^32 33^ Within each stratum, the participants are further assigned to either of the study arms with an intended ratio of 1:1 through random allocation.

Box 1List of eligibility criteriaInclusion criteria≥75 years.Living at home (ie not in nursing home).Emergency admission.Registered at one of nine specified primary care centres.Exclusion criteriaDo not speak Swedish or unable to communicate.Admitted due to intoxication (drug or alcohol).Scheduled for palliative care.

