#### Hospital readmissions

The primary outcome is time until unplanned drug-related readmission within 180 days of being discharged from the hospital. As a secondary outcome, we also study these events within a narrower time frame of 30 days. The cause of each readmission will be retrospectively determined by a group of blinded physicians and pharmacists who are not otherwise involved in the study. This assessment group will reach a consensus decision regarding the causality of each readmission according to criteria from WHO, a method that has been used previously in similar studies.^25 34 35^ Readmissions classified as certain, probable or possible in this assessment will be regarded as drug related in the following statistical analysis. We also measure time until unplanned hospital visit (all-cause readmissions and emergency department visits), time until death, as well as frequencies of unplanned drug-related hospital readmissions and unplanned hospital visits.

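### Randomisation is stratified on the cognitive scale, but the named primary log-rank and Cox comparison carries no stratification; stratifying it would be a small gain at no cost

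*Protocol article*

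**What the plan says.** Under Study population, recruitment and randomisation, the Protocol article states that "the participants are randomly assigned to one of the two study arms through a stratified randomisation procedure", and that this is "based on their results from a shortened 4-item version of the Gottfries" scale. Within each stratum, arms are assigned "with an intended ratio of 1:1 through random allocation". The cut-off, the number of strata and any blocking are not given in the text, and figure 1 is not available here.

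Under Hospital readmissions, the endpoint is fixed: "The primary outcome is time until unplanned drug-related readmission within 180 days of being discharged from the hospital".

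Under Statistics, the plan is to "analyse differences in survival data between the groups through log rank tests and Cox proportional hazard models". The sentence after it reads: "Further investigations of subgroup effects and adjustments of the regression models will be based on heart failure and cognitive impairment as prognostic factors". The Abstract has the same structure: log-rank and Cox for the primary outcome, then the sentence on subgroups and adjustment.

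**The concern.** When a factor is thought important enough to stratify the allocation, the primary analysis should normally carry it too. Here the first-named comparison, the log-rank test, is given without strata. The Cox model is listed beside it in the same plain form. The factor returns one sentence later as something to examine further, and only for regression models, so nothing in the text brings the randomisation stratum into the log-rank test.

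The article itself calls cognitive impairment prognostic. Its Introduction adds that the drug-related share of admissions appears higher in people with major neurocognitive disorder. If the strata do differ in risk, pooling them has three consequences:

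- some power is lost;
- the hazard ratio becomes a marginal one, slightly nearer 1 than the within-stratum value;
- if the arms are kept balanced inside strata, the usual log-rank variance is a little too large.

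What is at stake is a small amount of efficiency on the primary endpoint, and clarity about which of the listed results decides the trial.

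**Working it through.** **1. The plan's own figure.** Inputs from Statistics: control risk 0.19, relative reduction 40%, two-sided 0.05, power 80%, total 700. Intervention risk = 0.19 × 0.60 = 0.114; mean risk = 0.152.

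n per arm = [1.960·√(2 × 0.152 × 0.848) + 0.842·√(0.19 × 0.81 + 0.114 × 0.886)]² / 0.076² = [0.995 + 0.425]² / 0.005776 ≈ 349.1, so 350 per arm and 700 in total.

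The figure reproduces, with 80.1% power. With the rounded 11% instead, power at 700 is 84.4%. Stratifying the analysis leaves this calculation unchanged.

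**2. Hazard ratio, assuming constant hazards.** ln(1 − 0.114)/ln(1 − 0.19) = 0.574. Expected events: 700 × (0.19 + 0.114)/2 ≈ 106.

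**3. Power with two equal strata (assumed).** N = 700, hazard ratio 0.574, average control risk 19%. The stratum risks are assumptions, because the article gives none. The implied hazard ratios between strata are ln(0.74)/ln(0.88) ≈ 2.4 and ln(0.70)/ln(0.92) ≈ 4.3.

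| Control risks | Allocation within strata | Unstratified log-rank | Stratified | Gain (points) |
|---|---|---|---|---|
| 26% / 12% | balanced | 79.5% | 80.5% | 1.0 |
| 26% / 12% | simple | 79.4% | 80.1% | 0.7 |
| 30% / 8% | balanced | 77.7% | 80.0% | 2.3 |
| 30% / 8% | simple | 78.3% | 80.6% | 2.3 |

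A separate set of 6,000 trials per setting gave gains of 0.7 (79.9% vs 80.6%) and 2.4 (78.1% vs 80.5%). Further runs at 30%/8% scattered between 1.5 and 3 points.

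**4. Unequal strata.** Here 35% of participants are assumed to be in the impaired stratum, with blocks of four, risks of 19% vs 11%, and 10,000 trials per cell.

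| Hazard ratio between strata | Type I error, unstratified / stratified | Power, unstratified / stratified | Gain (points) |
|---|---|---|---|
| 1 | 4.96% / 4.94% | 84.85% / 84.77% | −0.08 |
| 1.5 | 4.63% / 4.77% | 84.53% / 84.70% | 0.17 |
| 2 | 4.60% / 5.00% | 84.19% / 84.73% | 0.54 |
| 3 | 4.37% / 5.06% | 83.46% / 84.71% | 1.25 |
| 4 | 4.17% / 5.39% | 83.17% / 85.43% | 2.26 |

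The Monte Carlo standard error of a 5% rejection rate is √(0.05 × 0.95/10,000) ≈ 0.22 points. The 5.39% is therefore compatible with 5%.

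**5. When is the unstratified test conservative?** With balanced allocation, the null z-statistic had a standard deviation of 0.977 (26%/12%) and 0.948 to 0.966 (30%/8%). Null rejection was 4.5% and 3.9%. With simple randomisation within strata, the standard deviations were 0.993 and 0.998 and rejection was 5.0% and 4.9%. The conservatism thus depends on balance within strata, whereas the power gain in step 3 does not.

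**6. Shift in the hazard ratio.** The marginal ratio over 180 days is ln(mean survival, intervention)/ln(mean survival, control).

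- 26%/12%: ln[(0.74^0.574 + 0.88^0.574)/2] / ln(0.81) = ln(0.885)/ln(0.81) ≈ 0.579.
- 30%/8%: ln[(0.70^0.574 + 0.92^0.574)/2] / ln(0.81) = ln(0.884)/ln(0.81) ≈ 0.585.

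The larger shift is ln(0.585/0.574) ≈ 0.019 on the log scale. The standard error of the log hazard ratio is about 2/√106 ≈ 0.19.

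**The case against.** The strongest reply is that the article does not disregard the factor. Cognitive impairment is one of two prespecified adjustment factors for the Cox model, and nowhere is the primary analysis called unstratified. Whether the log-rank test is stratified, how the scale is coded and which specification decides are details that an analysis plan commonly settles, and that plan is not shown. The effect is also small, and every stratum risk, share and count used to size it is assumed.

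Much of this stands. A reader might infer that the plan ignores its strata; the planned adjustment rules that out. A reader might also infer that the plan's standard errors are necessarily too large. That would require allocation balanced within strata, and the article states only an intended 1:1 ratio by random allocation. The shift in the hazard ratio is the difference between a marginal and a conditional quantity, so it is not an error, and it is about a tenth of a standard error.

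The reply does not dispose of the point. The article names its primary methods and places the stratification factor in a follow-on sentence that covers regression models only, in the Abstract as well as in Statistics. That is a stated arrangement with a better alternative that costs nothing, so it is more than absent detail. The power gain also persists under simple randomisation within strata.

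**Conclusion.** The point holds as a free improvement of small size. The primary comparison, as named, does not carry the factor on which randomisation is stratified. Under the assumed stratum shares and hazard ratios between strata of 1 to about 4.3, the cost is roughly 0 to 2.5 points of power, with well under 1 point to about 1 point at hazard ratios near 2. The hazard ratio moves from 0.574 to at most about 0.585. If the stratum is not prognostic, nothing is lost or gained.

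Two stronger conclusions are not supported. The trial's validity is not in doubt: omitting the strata does not inflate type I error, and the sample size of 700 is unchanged. Nor does the stratified design imply that heart failure belongs in the primary model, since it is not a randomisation factor.

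**What to change.** Add one sentence to Statistics: the primary log-rank test and Cox model are stratified by the cognitive-scale stratum used at randomisation, and this is the decisive analysis. State that cognitive impairment, where it is used for adjustment, means that same classification, or define the difference. Report the unstratified log-rank and Cox results, and the Cox model further adjusted for heart failure, as supportive.

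The cost is one sentence. The stratum is known for every randomised participant, diagnoses are already collected at baseline, and no extra participants are needed. With 161 of 700 randomised by November 2019, the choice can be recorded before any outcome analysis.

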### Data collection and outcomes

All outcome data will be gathered from medical charts with the exception of self-report questionnaires. All collected research data will be coded and kept in locked archives. Before, during and after the trial, all forms and protocols used during the interventions and follow-ups that reveal individual personal data are stored according to the same principle. There will be no identifiable data in the dissemination of the results. In summary, outcomes will be measured at the time of discharge from hospital (baseline) and then after 30 and 180 days, respectively (table 2). The follow-ups on Medication Adherence Report Scale (MARS-5) and EuroQuol five-dimension (EQ-5D) are conducted by phone and preferably in conjunction with the intervention phone calls. Rehabilitation needs require that some enrolled participants are transferred to the geriatric department before leaving the hospital for home. If a participant is relocated to another clinical ward, the actual discharge from hospital will be considered as baseline, with the exception of self-reported adherence and quality of life, which are reported on the original ward. As a consequence, we contact all study participants by phone at 30 and 180 days after their first report regarding MARS-5 and EQ-5D, even if this date differs from the actual date on which they were discharged from hospital.

**Table 2 T2:** Scheduled data collection for primary and secondary outcomes

	Baseline	30 days	180 days

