**Patient characteristics**			
Age and sex	x		
Cohabitant and home healthcare	x		
Diagnoses	x		
No of medications	x		

Baseline data are collected from the date of hospital discharge. The data for MARS-5 and EQ-5D can be retrieved before the participants are discharged and the date on which questionnaires are completed are considered as baseline regarding these two outcomes.

EQ-5D, EuroQuol five-dimension; MARS-5, Medication Adherence Report Scale.

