#### Medication adherence

We measure study participants’ self-reported medication adherence using the MARS-5, a self-assessment questionnaire with five items on a five-point scale that has previously been translated into Swedish.^36 37^

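### Only unadjusted tests are named for the secondary outcomes, although MARS-5 and EQ-5D have a scheduled pre-randomisation value that ANCOVA would turn into precision

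*Protocol article*

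**What the plan says.** **Timing of the questionnaires.** Under Study population, recruitment and randomisation, once consent is obtained "the participants report self-assessed adherence and quality of life through questionnaires"; random assignment follows discharge from the ward. Data collection and outcomes gives the general schedule: "outcomes will be measured at the time of discharge from hospital (baseline) and then after 30 and 180 days, respectively". Table 2 marks both MARS-5 and EQ-5D at all three times, and its note says that "the date on which questionnaires are completed are considered as baseline regarding these two outcomes". A pre-randomisation value is therefore scheduled for both instruments.

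**Scales.** MARS-5 is described as "a self-assessment questionnaire with five items on a five-point scale". EQ-5D has two parts: five descriptive dimensions and a visual analogue scale (VAS) from 0 to 100.

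**Randomisation.** Allocation is 1:1 within strata defined by the 4-item version of the Gottfries' Cognitive Scale.

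**Analysis.** The Statistics section says: "We will analyse secondary outcomes using various appropriate statistical tests". Its two examples are the chi-square test and an "independent sample t-test, depending on the type of variable". Adjustment appears once, directly after the survival methods: "adjustments of the regression models will be based on heart failure and cognitive impairment as prognostic factors". A baseline questionnaire score is not among the covariates.

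**The concern.** A two-sample t-test has no place for a covariate. On follow-up scores it uses neither the baseline value nor the stratification factor. On change scores it uses the baseline, but with a fixed slope of one. Adherence and quality of life are declared secondary objectives, so their confidence intervals matter to the reader of the results. If the named example is carried into the analysis of MARS-5 and the EQ-5D VAS, those intervals may be wider than the scheduled data require.

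The article also does not say whether a t-test would be run on follow-up or change scores. The two give different estimates from the same data, and their precision differs.

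**Working it through.** **1. The plan's own figure.** The only sample-size figure is 700, for drug-related readmission. Inputs from Statistics: 19% in controls, a 40% relative reduction (0.6 × 19% = 11.4%, printed as 11%), 80% power, two-sided 0.05. With the pooled-variance formula for two proportions and p̄ = (0.19 + 0.114)/2 = 0.152:

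n per arm = [1.960 √(2 × 0.152 × 0.848) + 0.842 √(0.19 × 0.81 + 0.114 × 0.886)]² / 0.076² → 350, or 700 in total.

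The figure is reproduced and does not depend on the questionnaires. No standard deviation, target difference, correlation or power is stated for MARS-5 or EQ-5D.

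**2. Variance of the three analyses.** Let r be the correlation between baseline and follow-up score, with equal variance at the two times. Relative to a t-test on follow-up scores:

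- ANCOVA: 1 − r²
- t-test on change scores: 2(1 − r)

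The change-score factor minus the ANCOVA factor is 2(1 − r) − (1 − r²) = (1 − r)², which is never negative. Put differently, follow-up scores fix the slope on baseline at 0 and change scores fix it at 1, while ANCOVA estimates the best slope. With hundreds of participants, the degree of freedom spent is negligible.

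**3. Numbers.** The article gives no r, so 0.3 to 0.7 is an assumption. With 350 per arm, all analysed, the t-test on follow-up scores has 80% power at a standardised difference of (1.960 + 0.842) × √(2/350) = 0.212. Power at that same difference is Φ(2.802/√factor − 1.960).

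| Assumed r | ANCOVA variance | Change-score variance | ANCOVA power | Change-score power | Difference detectable by ANCOVA (80% power) | Unadjusted N matching ANCOVA on 700 |
|---|---|---|---|---|---|---|
| 0.3 | 0.91 | 1.4 | 83.6% | 65.8% | 0.202 | 769 |
| 0.5 | 0.75 | 1.0 | 89.9% | 80.0% | 0.183 | 933 |
| 0.7 | 0.51 | 0.6 | 97.5% | 95.1% | 0.151 | 1373 |

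The detectable difference is 0.212 × √(1 − r²); the matching N is 700/(1 − r²).

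**4. Fewer questionnaires.** Current trial status reports 44 of 161 discontinued (27.3%). Used purely as an illustration of missing questionnaires, this leaves 350 × (1 − 0.273) = 254 per arm. The detectable difference is then 0.249 by t-test on follow-up scores, and 0.237, 0.215 and 0.178 by ANCOVA at the three values of r. The relative gain is the same.

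**The case against.** The strongest reply is that the article decides nothing here. The t-test is an example, the wording defers to the type of variable, and neither scale is assigned to it. A condensed article commonly leaves the model for each secondary outcome to an analysis plan, which may exist and is not shown. A reader might infer that the plan commits MARS-5 and EQ-5D to a t-test that ignores baseline. The text does not support this: a t-test on change scores fits the wording equally well and does use the baseline.

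That limits the point without removing it. Both tests named are unadjusted, baseline adjustment of these scores is mentioned nowhere, and in large samples either version of the t-test is at best as precise as ANCOVA. Below r = 0.5, the change-score version is less precise than leaving the baseline out.

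Other limits also stand:

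- Under randomisation the unadjusted t-test is valid and unbiased. Chance baseline imbalance is part of the sampling error its interval already reflects, so it is not a separate bias.
- A reader might take the baseline as available for everyone. That is only the schedule; no completion rate is given.
- No EQ-5D index is mentioned, and the five dimensions are categorical. The argument applies to the VAS and the MARS-5 score.
- The gain is modest at low correlation: 3.6 percentage points of power at r = 0.3.
- Discontinuations and deviations from the protocol applies last observation carried forward to outcomes other than time to event. Where a baseline value is carried forward, baseline and follow-up coincide. This raises the observed r artificially and makes the ANCOVA gain look larger than it is.

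**Conclusion.** The point holds as an available improvement in precision for secondary outcomes. The article names only unadjusted tests where the scheduled data allow a baseline- and stratum-adjusted comparison. At assumed correlations of 0.3, 0.5 and 0.7, ANCOVA reduces variance by 9%, 25% and 49% relative to a t-test on follow-up scores. Relative to change scores the variance ratio is 0.91/1.4 = 0.65, 0.75/1.0 = 0.75 and 0.51/0.6 = 0.85.

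These sizes rest on the assumed r, equal variance at the two times, a linear relation with baseline, and a baseline value for those analysed. The ordering of the methods does not depend on r. Any further gain from the cognitive stratum cannot be sized from the article.

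It would be wrong to conclude that the secondary results would be biased or invalid. The primary analysis and the sample size of 700 are untouched. ANCOVA also does not address the bias from unblinded self-report that the article acknowledges for these two instruments.

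**What to change.** Add to Statistics: the MARS-5 score and the EQ-5D VAS at 30 and 180 days will be compared between arms by ANCOVA, adjusted for the baseline value of the same instrument and for the cognitive stratum used in randomisation, and reported as an adjusted mean difference with 95% CI.

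If a repeated-measures mixed model is preferred, reconcile it with the last-observation-carried-forward rule in Discontinuations and deviations from the protocol, because the two handle missing follow-ups differently. With either model, say how a missing baseline score is handled.

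If the analysis plan already specifies this, aligning the article's sentence with it is enough. The cost is wording: no new data, no extra visits and no change to the sample size. By November 2019, 161 of the 700 had been randomised, so the choice could be fixed well before analysis.

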### Limitations and risk of bias

The first and second author of this protocol are involved in the trial both as researchers and as clinical pharmacists conducting the intervention. As previously mentioned, we will undertake several measures to reduce the risk of bias that could emerge from these multiple roles. For example, we will consult external staff for the primary outcome assessment and statistical analyses. Other clinical outcomes in terms of all-cause readmissions, emergency department visits and mortality are electronically documented data with no room for subjectivity. Therefore, this risk of bias mainly applies to MARS-5 and EQ-5D, which should be considered in the interpretation of our findings. Moreover, all interviews within the qualitative part of the study will be conducted by another person than the clinical pharmacist who performed the interventions on those specific participants. Due to the nature of the intervention, neither participants nor clinical pharmacists are blinded. We do not consider the lack of blinding to be a major issue for the study, but bias related to special attention and the knowledge of being observed could possibly affect self-reported adherence and quality of life among the participants.

## Ethics and dissemination

Prior to hospital discharge, people who fulfil the inclusion criteria are given oral and written information about the study on the clinical ward. Anyone who does not wish to participate is free to decline or withdraw at any time during the course of the trial. Individuals with major NCD participate without formal written informed consent, although in these cases both the intended participant and the next of kin are informed about the study and given the opportunity to decline participation. The study has been approved by the Regional Ethical Review Board in Umeå (registration numbers 2017-69-31M, 2018-83-32M and 2018-254-32M). No participant in this trial is subject to any clinical procedures that are likely to be harmful and there are therefore no routines for collecting, assessing, reporting or managing adverse events or other unintended effects of the intervention. Moreover, we assume that any participants who are uncomfortable with the trial will exercise their right to withdraw from the protocols. There are no agreements or other regulations that will limit our access to collected data. The study will be reported according to the Consolidated Standards of Reporting Trials guidelines.^41^ Our intention is to publish the results with open access in international peer-reviewed journals. We also aim to present the results of the trial at both national and international conferences. The trial is expected to result in more than one published article and form part of two PhD theses. In accordance with the guidelines issued by the International Committee of Medical Journal Editors,^42^ all listed authors have been involved in developing or revising the study design, contributed in the review process of this article, approved the final version and will ensure that issues related to the accuracy or integrity of the work are investigated and resolved.

